### **Analysis of primary endpoint**

Statistical analysis of the primary outcome indicators was conducted using the ITT dataset and the PP dataset. The baseline measurements of the study subjects were adjusted using GEE model to compare the intervention effects in each group. At a single time point, the intergroup differences at baseline, 6-week postintervention, and during 12-week follow-up are compared using independent sample t-tests or Mann-Whitney U tests.

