cognitive function in older adults with sleep disorder and MCI, using a sham-controlled, double-blind intervention design. We assessed sleep quality and cognitive function at the 6-week postintervention and 12-week follow-up.

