### **Outcomes**

The outcome indicators of this study will be evaluated at baseline assessment (before intervention), 6-week after intervention, and at the 12-week follow-up. Each patient

underwent a series of neuropsychological assessments to evaluate their cognitive level and sleep status. The examinations were conducted in accordance with a unified implementation plan and standard operating procedures.

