### **Primary Outcomes**

**Sleep quality assessment:** Use the internationally recognized Pittsburgh Sleep Quality Index (PSQI) to assess the sleep quality of the subjects in the past month. The PSQI scale consists of 19 self-assessment items, comprising 7 dimensions: sleep quality, sleep onset latency, sleep duration, sleep efficiency, sleep disturbances, use of sleep medication, and daytime dysfunction. Each dimension is scored on a scale of 0-3, with the cumulative score of all dimensions representing the total PSQI score, which ranges from 0 to 21. A higher score indicates poorer sleep quality.

**Global cognitive function:** The Montreal Cognitive Assessment (MoCA) (FuZhou Edition) was used to assess the Global cognitive function of patients. which includes 8 cognitive domains and 11 examination items covering visuospatial and executive functions, naming, memory, attention, language, abstraction, delayed recall, and orientation. The MoCA score ranges from 0 to 30, with higher scores indicating better overall cognitive function. If the education level is  $\leq 12$  years, an additional point is added to the total score, and a score of  $< 26$  indicates mild cognitive impairment (MCI).

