### Data management and general analysis

A comparison of baseline characteristics of the selected subjects in the two groups was conducted to assess comparability. Intervention effect evaluation included determining

intervention effect indicators and comparing intervention effects between groups. The primary outcome evaluation used the ITT dataset as the main dataset for intervention effect evaluation and the PP dataset for sensitivity analysis. Secondary outcome indicators were evaluated using the PP dataset. Safety assessment included statistical analysis of adverse events such as dizziness and falls, with the SS dataset used for safety assessment.

All statistical analyses were performed using SPSS 24.0 software. Two-tailed tests were used for statistical analysis, the primary outcome indicator is  $P < 0.025$  and the secondary outcome indicator is  $P < 0.05$  are considered statistically significant in comparison between groups. Continuous data were presented as means, standard deviations, or medians, and interquartile ranges depending on the normality of distribution. Categorical data were presented as frequencies (percentages). Normality tests were conducted for variable distributions, and independent sample t-tests were used for intergroup comparisons of normally distributed continuous data. Non-parametric tests were used for statistical analysis of non-normally distributed continuous data. Chi-square tests were used for comparisons of categorical variables, with the Fisher exact probability test used when necessary.

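### No primary visit or deciding test is named for PSQI and MoCA; if either visit can count as a primary success, the family-wise error is about 7% to 9.5%, not the 5% that the 0.025 threshold implies

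*Combined protocol and SAP*

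**What the plan says.** The *Primary Outcomes* section lists two measures and gives neither a visit: "Use the internationally recognized Pittsburgh Sleep Quality Index (PSQI) to assess the sleep quality of the subjects in the past month" and "The Montreal Cognitive Assessment (MoCA) (FuZhou Edition) was used to assess the Global cognitive function of patients". The closing sentence of the background gives the two post-baseline assessments equal weight: "We assessed sleep quality and cognitive function at the 6-week postintervention and 12-week follow-up". The *Outcomes* section does the same: "The outcome indicators of this study will be evaluated at baseline assessment (before intervention), 6-week after intervention, and at the 12-week follow-up". Table 1 schedules both measures at T2 and T3.

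In the SAP, *Data management and general analysis* sets 0.025 for primary and 0.05 for secondary outcome indicators. Results below these limits "are considered statistically significant in comparison between groups". It also states that "Two-tailed tests were used for statistical analysis".

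*Analysis of primary endpoint* prescribes two kinds of analysis. One is a GEE adjusted for baseline, with no term, contrast or visit named as decisive. The other is by visit: "At a single time point, the intergroup differences at baseline, 6-week postintervention, and during 12-week follow-up are compared using independent sample t-tests", with Mann-Whitney tests as the alternative. No section orders the visits, corrects across them, makes one depend on the other, or requires success at both.

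**The concern.** A limit of 0.025 is half of 0.05, and there are two primary outcomes. The natural reading is a Bonferroni split that pays for one test per outcome. The primary-endpoint section then provides two post-baseline between-group tests per outcome, plus a GEE, without saying which of them carries the claim.

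Two things are at stake. If any one of several results can be reported as a primary success, the error rate that the split appears to protect is exceeded. And with neither visit nor test fixed, the headline result can be chosen after the data are seen. That second harm does not depend on any assumed correlation.

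**Working it through.** **Inputs from the documents.** Two primary outcomes (*Primary Outcomes*). Two post-baseline visits (*Outcomes*, Table 1). Two-sided 0.025 per primary comparison (*Data management and general analysis*). The baseline comparison is not an efficacy test and is not counted. The per-protocol analysis is labelled a sensitivity analysis for the primary outcomes and is not counted either.

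**Inputs assumed.** The documents give no correlations. Let *r_t* be the correlation between test statistics at the two visits within an outcome, and *r_b* that between the two outcomes at the same visit. The correlation across both outcome and visit is taken as *r_t* × *r_b*.

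**1. The plan's threshold.** 0.05 / 2 = 0.025. With one test per outcome, the family-wise error is at most 2 × 0.025 = 5%. If the tests are independent it is 1 − (1 − 0.025)² = 4.9%. So 0.025 fits two tests.

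**2. Four tests (two outcomes × two visits), any one sufficing.** The upper bound is 4 × 0.025 = 10%. If independent, the error is 1 − (1 − 0.025)⁴ = 9.6%. With correlation, simulation of four normal statistics (2,000,000 draws, reject if any |z| > 2.241) gives:

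| *r_t* | *r_b* = 0 | *r_b* = 0.3 | *r_b* = 0.5 |
|---|---|---|---|
| 0.3 | 9.4% | 9.2% | 8.9% |
| 0.5 | 9.1% | 8.9% | 8.5% |
| 0.7 | 8.4% | 8.2% | 7.9% |
| 0.8 | 7.9% | 7.7% | 7.4% |
| 0.9 | 7.1% | 6.9% | 6.7% |

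With one visit per outcome, over the same *r_b* values, the error is 4.7% to 5.0%. The excess disappears only as *r_t* approaches 1.

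**3. Is naming a visit enough?** Suppose only T2 counts, but a claim may rest on either the baseline-adjusted or the unadjusted comparison, each at 0.025. If ρ is the baseline-to-T2 correlation, the two statistics correlate at √(1 − ρ²): 0.87 at ρ = 0.5 and 0.71 at ρ = 0.7. Simulating both outcomes with ρ from 0.5 to 0.7 and *r_b* from 0 to 0.5 (2,000,000 draws) gives 6.9% to 8.4%. The test must therefore be named as well as the visit.

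**4. Ordering the visits or splitting alpha again.** If T3 of an outcome is tested only after that outcome's T2 test succeeds, each outcome's chain has error at most 0.025, and the total is at most 5% under any correlation. Four tests at 0.0125 also hold 5%, but cost power. Using the Tai Chi figures in *Sample size*, the pooled SD is √((1.52² + 2.59²)/2) = 2.12 and d = 1.22 / 2.12 = 0.575. With 49 per group, t-test power is 0.80 at 0.05 (the plan's own figure), 0.71 at 0.025 and 0.62 at 0.0125. This covers PSQI only; the documents give no inputs for MoCA.

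**The case against.** The strongest reply is that the GEE is the primary analysis. *Covariates and subgroup analysis* assigns GEE to the primary and secondary outcomes, and the primary-endpoint section puts it first. The by-visit sentence follows it and includes baseline, where no treatment effect can exist, so it may be meant as supporting description. If the GEE yields one overall group effect per outcome, there are two tests at 0.025 and no inflation. This reading is open and cannot be dismissed. But the SAP does not state it: no GEE effect is named, the by-visit tests are not called supportive, and the 0.025 limit is attached to between-group comparisons generally. Even on this reading, someone must still choose among an overall effect, a group-by-time term and a visit contrast.

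It is also fair to say that no section states a family-wise target or that one significant result makes the trial positive. The 5% is inferred from 0.05/2, from the looser 0.05 limit for secondary outcomes, and from the 0.05 used for sample size. The inference is reasonable, but it remains an inference.

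A reader might go further and infer that this trial's family-wise error simply is 7% to 9%. The documents do not support that. The figure depends on letting either visit decide and on correlations that they do not give.

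**Conclusion.** The gap is real: the SAP specifies neither the primary visit nor the deciding test for PSQI and MoCA. The size is conditional. If success at either visit counts, the family-wise error is about 7% to 9.5% for visit correlations of 0.3 to 0.8 and outcome correlations of 0 to 0.5, bounded by 10%, against an inferred 5%. If one test per outcome decides, such as a single GEE effect, it stays within 5%. The text does not settle which applies, and that lack of definition is the firm part of the finding. Nothing here shows that a particular visit or test was, or will be, picked to suit the results.

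**What to change.** In *Primary Outcomes*, *Data management and general analysis* and *Analysis of primary endpoint*:

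- Name one deciding test per outcome at two-sided 0.025: the baseline-adjusted GEE group contrast at one pre-named visit, for example T2, the end of the 6-week intervention. The documents do not rank the visits, so T2 is an example; naming T3 first, or one visit-averaged GEE effect, would also control the error.
- If T2 is chosen, test the same contrast at T3 at 0.025 only when that outcome's T2 contrast is significant. Otherwise report T3 as an estimate with an interval.
- Label the single-time-point t-tests and Mann-Whitney tests, including baseline, as descriptive, with no significance claim.
- Reconcile the timing of T3: *Study Design* places it 12 weeks after the intervention ends, while Table 1 labels it week 12.

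The change needs no new data or participants. Its price is that a difference seen only at T3 could no longer be claimed as a primary success. Timing also matters. *Study Design* dates the trial October 2022 to February 2024, and parts of the SAP are in the past tense. The choice must be made before unblinded results are seen, or else be reported as post hoc.

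### No primary visit, GEE contrast or deciding method is named for PSQI and MoCA, so P < 0.025 holds 5% overall only if one test per outcome counts

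*Combined protocol and SAP*

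**What the plan says.** The protocol names two primary outcomes under Primary Outcomes: PSQI total score ("Use the internationally recognized Pittsburgh Sleep Quality Index (PSQI) to assess the sleep quality of the subjects in the past month") and MoCA ("The Montreal Cognitive Assessment (MoCA) (FuZhou Edition) was used to assess the Global cognitive function of patients"). The Outcomes section has them measured at baseline, "6-week after intervention, and at the 12-week follow-up". No visit is ranked above another there, in Study Design, or at the end of the background section.

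SAP, Data management and general analysis: "Two-tailed tests were used for statistical analysis", and for between-group comparisons "the primary outcome indicator is $P < 0.025$ and the secondary outcome indicator is" held to 0.05. The section ranks the analysis sets for the primary outcomes (ITT main, PP as sensitivity) but does not rank visits or methods.

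SAP, Analysis of primary endpoint, gives two routes. The first is a model: "The baseline measurements of the study subjects were adjusted using GEE model to compare the intervention effects in each group". The second is a set of comparisons at each time point: "the intergroup differences at baseline, 6-week postintervention, and during 12-week follow-up are compared using independent sample t-tests or Mann-Whitney U tests". Covariates and subgroup analysis also names GEE for the primary and secondary outcomes, with baseline values and the IPAQ as covariates. Neither section says whether the GEE result of interest is an average over visits, an arm-by-visit term or the difference at one visit.

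**The concern.** A threshold of 0.025 for each of two outcomes is enough when each outcome has one deciding test. Here each outcome has a between-arm comparison at two post-baseline visits, by an unadjusted test and potentially also from the GEE. All of these sit under the primary endpoint heading, and none is labelled descriptive.

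Two things are at stake. If any of these results may carry a primary claim, the chance of at least one false claim exceeds 5%. And if 6 weeks and follow-up disagree, or the adjusted and unadjusted results disagree, the plan does not say which is the trial's answer. The choice could then be made after the results are known.

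**Working it through.** **Inputs from the documents.** Two primary outcomes; two post-baseline visits; two methods (baseline-adjusted GEE; t-test or Mann-Whitney test at a visit); two-sided 0.025 per primary comparison. The baseline comparison is not an efficacy test and is not counted. ITT and PP are ranked, so PP is not counted either.

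**Assumed inputs.** The documents give no correlations between visits, between outcomes or with baseline. These are varied below.

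**Step 1: the plan's own threshold.** 0.05 / 2 = 0.025. With one test per outcome the bound is 2 × 0.025 = 0.050, and with independent tests 1 − 0.975² = 0.0494. The Sample size section supports an overall level of 5%: with α = 0.05 two-sided, power 0.80, difference 12.48 − 11.26 = 1.22 and pooled SD √[(1.52² + 2.59²)/2] = 2.123 (d = 0.575), a two-sample t-test needs 49 per group. Then 49 / 0.9 rounds up to 55, as stated.

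**Step 2: two outcomes × two visits, one method (4 tests).** Bound: 4 × 0.025 = 0.100. Independent: 1 − 0.975⁴ = 0.0963. With correlation, the error rate is the probability that at least one of four standard normal statistics exceeds the two-sided 0.025 critical value under the global null. It was simulated with 1,000,000 draws per setting:

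| Between-visit correlation (assumed) | Between-outcome correlation 0 | 0.2 | 0.4 |
|---|---|---|---|
| 0.3 | 0.094 | 0.093 | 0.091 |
| 0.5 | 0.091 | 0.091 | 0.087 |
| 0.7 | 0.084 | 0.084 | 0.081 |
| 0.9 | 0.071 | 0.070 | 0.068 |
| 1.0 | 0.049 | 0.049 | 0.048 |

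The rate returns to about 5% only when the two visits are perfectly correlated.

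For baseline-adjusted contrasts the relevant figure is the correlation left after baseline is removed. If both visits correlate b with baseline and r with each other, it is (r − b²)/(1 − b²). For b = 0.5 and r = 0.7 that is 0.45 / 0.75 = 0.60. Adjustment therefore moves the result towards the upper rows of the table.

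**Step 3: both methods also count (8 tests).** Bound: 8 × 0.025 = 0.200. Independent: 1 − 0.975⁸ = 0.183. Simulated with assumed baseline correlation 0.3 to 0.7, between-visit correlation 0.5 to 0.7 and between-outcome correlation 0 to 0.3, the rate runs from 0.107 to 0.155.

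**Step 4: after a fix.** One named contrast per outcome: 2 × 0.025 = 0.05. Both visits primary with one method: 0.05 / 4 = 0.0125 per test. A fixed sequence within each outcome spends 0.025 on that outcome, so again 2 × 0.025 = 0.05.

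**The case against.** The best defence is that GEE is the planned model. Covariates and subgroup analysis prescribes it, and Analysis of primary endpoint puts it first and the single-visit comparisons second. On that reading the t-tests and Mann-Whitney tests only illustrate the model. If one GEE test per outcome decides, 0.025 keeps the overall error at 5% or less. This is a fair reading and it limits the point. It does not remove it: the SAP never states the ranking, and a GEE with two post-baseline visits yields more than one arm effect, none of which is named.

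A reader might go further and infer one of the following. The documents do not support them.

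- *The plan demonstrably fails to control error at 5%.* No family-wise target is stated; it is inferred from 0.05 / 2 and from the α of 0.05 in the sample size. Nor does any rule say that a win at either visit is a success. The plan does not exclude that rule, so the inflation is conditional.
- *Choosing between t-test and Mann-Whitney after a normality check multiplies the tests.* It still gives one test at each visit, so it does not add to the count.
- *The baseline comparison inflates the error.* It makes no efficacy claim.
- *6 weeks is the only proper primary visit.* Nothing ranks it above follow-up; several choices control the error.

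**Conclusion.** The point holds as a gap in specification with a conditional cost. The primary visit, the GEE contrast and the role of the single-visit tests are not stated, so the 0.025 threshold covers fewer tests than the plan sets out. If either visit may support a primary claim, the family-wise error is up to 10%, and about 7% to 9.5% for assumed between-visit correlations of 0.9 to 0.3. If adjusted and unadjusted results both count, it is about 11% to 15.5% under the assumptions in the working. If one test per outcome decides, it is at most 5%. The size rests on an inferred 5% target, an inferred either-visit success rule and assumed correlations. The absence of a defined answer when visits or methods disagree rests on none of these.

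**What to change.** In Analysis of primary endpoint:

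1. Name one baseline-adjusted GEE contrast per outcome as the primary test, at two-sided 0.025 each. An example is the between-arm difference at 6 weeks from a model with an arm-by-visit term, with follow-up secondary.
2. If both visits are to stay primary, either test each at 0.0125 or use a fixed sequence within each outcome: the second visit is tested at 0.025 only if the first is significant.
3. State that the single-visit t-tests and Mann-Whitney tests are supportive and carry no significance claim.
4. State that 0.025 is 0.05 divided over two outcomes, if that is the intention.
5. Reconcile the follow-up visit before naming any contrast that uses it. The Study Design text counts 12 weeks from completion of treatment, which is week 6 + 12 = 18. Table 1 places T3 at week 12.

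**Timing.** Study Design dates the trial October 2022 to February 2024, and much of the SAP is in the past tense. The choice should be fixed before unblinding. If unblinding has happened, report when the choice was made, because wording added afterwards cannot restore prespecified control.

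**Cost.** SAP wording only. A visit or method not named as primary can no longer support a primary claim on its own. Splitting alpha over visits lowers power per test. With the PSQI planning effect, 49 evaluable per group and the normal approximation Φ(d√(n/2) − z), power falls from Φ(2.84 − 2.24) ≈ 73% at 0.025 to Φ(2.84 − 2.50) ≈ 64% at 0.0125, before any gain from baseline adjustment.

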### **Analysis of secondary endpoints**

Statistical analysis of the secondary outcome indicators was performed using the PP dataset. The baseline measurements of the study subjects were adjusted using a generalized estimating equation model to compare the intervention effects in each group. At a single time point, the intergroup differences at baseline, 6-week postintervention, and during 12-week follow-up are compared using independent sample t-tests or Mann-Whitney U tests.

### **Safety**

During the study, any accidental injuries and acute illnesses will be recorded as Adverse Events (AEs). AEs will be classified as mild, moderate, or severe. Serious Adverse Events (SAEs) are events that result in life-threatening conditions, require hospitalization, or lead to persistent severe disabilities. All AEs and SAEs that are accidental or potentially related to the study will be reported to the Ethics Committee. The researchers will document the severity of symptoms, occurrence time, duration, and treatment measures in the Case Report Form (CRF) and assess their relevance to the intervention training.

### **3、 Quality Control**

#### **Quality Control for Researchers**

Before the start of the project, a detailed research manual will be developed and all researchers will undergo centralized and unified training to ensure the quality of the project's completion. This training will ensure that recruitment personnel are familiar with the recruitment process, screening, and inclusion/exclusion criteria; assessment personnel are proficient in the standardized assessment and calculation rules for outcome measures; objective sleep quality data is collected in a standardized manner; supervisory personnel are on-site to oversee training sessions and record participant attendance; and data entry personnel perform double entry and verification of data. Each step of the process will be executed by designated personnel who will not participate in other aspects of the study.

#### **Quality Control for Participants**

All participants will be strictly screened based on the inclusion and exclusion criteria, and those who do not meet the criteria will be excluded, with the number of exclusions and reasons for exclusion recorded. Prior to the start of the study, each participant will be provided with a detailed explanation of all experimental tasks and intervention methods, to address any concerns and provide free sleep, cognitive testing, and health consultations. Participant informed consent will be obtained.

#### **Quality Control for Intervention Processes**

During the Tai Chi training sessions, professional coaches will provide on-site teaching and guidance, promptly correcting any improper movements. Researchers will oversee each training session in its entirety, implementing an on-site sign-in system to track attendance. Participants who cannot attend scheduled training sessions on time are required to submit advance leave requests, with reasons for leave recorded. Participants who temporarily cannot attend centralized training sessions are instructed to practice at home using the day's teaching video and submit recorded practice videos to the Tai Chi coach for feedback. Tai Chi training sessions will be conducted in appropriate venues based on weather conditions to enhance participant compliance.

During rTMS treatment, the operation of the rTMS device must be performed by qualified rehabilitation therapists, the researchers promptly observe the participant's response and record the treatment intensity, frequency, and adverse reactions. Additionally, during the treatment, measures were taken to ensure that patients could not differentiate between the real and sham coils based on appearance, sound, or the sensation of stimulation, thereby maintaining blinding for the patients. Due to the specific settings and adjustments required for the equipment during operation, the therapists were aware of whether they were using an active coil or a sham coil while delivering stimulation. This was done to ensure the smooth conduct of the experiment. However, for the evaluators, we ensured that they were completely

unaware of the status of the coils, as their sole responsibility was to collect and analyze the data.

